### Outcomes

The primary outcomes will be reductions in body weight and BMI from baseline and reduction or maintenance of the prescribed energy and macronutrient intake during the 4-week intervention. The secondary outcomes will be reduced hunger, desire to eat, and food craving scores compared with baseline; reductions in fasting and postprandial responses of plasma glucose, insulin, GA, hunger hormones such as ghrelin; and an increase in the blood levels of hormones that participate in the regulation of satiety, such as PYY_3–36,_ GLP-1, and PP [47]. These hormones will be measured to understand mechanisms behind a possible effect of tDCS in weight, desire to eat, food cravings, or glycemic control and variability.

The exploratory outcomes will include the number of participants achieving a 3% reduction or more in body weight compared with baseline; improvements in insulin sensitivity and β-cell function compared with baseline; changes in body composition, such as reduced waist and hip circumferences and reduced body fat mass, compared with baseline; changes in glycemic variability, such as reduced MAGE compared with baseline; changes in depression and anxiety scores compared with baseline; and acute changes in subjective feelings of desire to eat, mood, and attention between pre- and post-tDCS sessions.

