**Methods/design:**

Overweight or obese adults between 20 and 50 years of age with stable weight over the last 4 months will be selected for a 4-week randomized clinical trial of fixed-dose tDCS (20 sessions; 5 consecutive weekdays/wk, 2 mA, 20 minutes) over the right dorsolateral prefrontal cortex associated with a weight loss diet. The subjects will be randomly assigned in a 1:1 ratio and stratified by sex to active tDCS + diet or sham tDCS + diet. The study will be conducted at the Endocrine and Metabolism Unit of the Hospital de Clínicas de Porto Alegre, Brazil. The primary outcome is weight loss. Energy and macronutrient consumption, as well as adherence to the diet, will be assessed using 3-day weighed dietary records. Changes in blood glucose and plasma insulin will be assessed, and participants will complete self-report questionnaires to assess changes in mood and food behavior. All analyses will be done on a per-protocol and intention-to-treat basis.

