#### Anthropometric assessment

Anthropometric assessment will be performed with the participants barefoot and wearing light clothing. Height will be measured using a wall-mounted stadiometer and recorded to the nearest 0.1 cm. An InBody 230 tetrapolar body composition analyzer (InBody, Seoul, South Korea) will be used to measure body weight and composition via bioelectrical impedance. This procedure will be performed in the morning, with the participant fasting and having avoided exercise in the last 24 hours. BMI will be calculated as weight (kg)/height (m^2^). Mid-upper arm circumference will be measured at the midpoint of the upper right arm, between the acromion process and the tip of the olecranon. Waist circumference will be measured midway between the lowest rib margin and the iliac crest, near the umbilicus. Hip circumference will be measured at the maximal gluteal protrusion. Flexible, nonstretch fiberglass tape will be used for these measurements.

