##### Hypocaloric diet

The energy deficit will be calculated for each participant individually using the online Body Weight Planner program, which is a validated dynamic simulation model of human metabolism recommended by the National Institute of Diabetes and Digestive and Kidney Diseases for prescribing weight loss diets [52]. Using the information on age, sex, height, weight, and physical activity level, the number of kilocalories per day needed to alter a specific amount of weight in a certain number of days can be determined.

The prescribed hypocaloric diets will conform to American Diabetes Association specifications for overweight or obese patients with type 2 diabetes or prediabetes. The planned macronutrient profile will be 45–50% of total energy intake as carbohydrates, with emphasis on a low glycemic index; 15–25% as protein; ≤ 30% from fat, with unsaturated fats being the main source (saturated fat limited to < 7%); and ≥ 20 g/d or 14 g/1000 kcal/d as fiber [53].

Compliance with this diet and changes in food consumption from baseline will be assessed using the 3-day WDR technique at three different times: at baseline, as described in the “Eating behavior assessment” section above, at the end of the first 2 weeks, and again during the last 2 weeks of the study, totaling nine WDRs. The diet composition, obtained from the prescribed diet and from the 3-day WDRs, will be analyzed (U.S. Department of Agriculture table [54]) in NutriBase 17 Pro Edition software (version 17.2; CyberSoft, Inc., Phoenix, AZ, USA). The mean values for energy and nutrients consumed during the 3-day WDR will be calculated. Patients will be classified as adherent or nonadherent according to whether or not they will reach their calculated energy goals and diet recommendations.

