#### Data analysis

To compare the participants’ baseline characteristics, Student’s *t* test and the chi-square test will be used as appropriate. The results will be expressed as mean ± SD, mean (95% CIs), or the number of patients with the characteristic (percent). The Shapiro-Wilk test will be used to verify data normality; variables with non-Gaussian distribution, such as insulin and the HOMA index, will be logarithmically transformed before analysis when necessary. The aRMR will be performed using logarithmically transformed data, as recommended by Kaiyala and Schwartz [40].

The effects of tDCS between groups over time will be analyzed using the generalized estimating equation (GEE), including tDCS group, time, and the group- and subgroup-by-time interaction as predictors. All GEE models will be followed by a Bonferroni post hoc analysis and the least significant difference test to identify significant differences detected by the GEE. Gamma distribution with log link function will be used for variables with non-Gaussian distribution. After treatment of the first ten participants, an interim security analysis was planned, and the trial may be stopped prematurely because of safety concerns, such as severe psychiatric and neurologic reactions. The outcomes will be presented as *p* values for the included factors and estimated marginal means, with corresponding 95% CIs for each tDCS group at each time point. A *p* value < 0.05 will be considered statistically significant. IBM SPSS Statistics version 19.0 statistical software (IBM, Armonk, NY, USA) will be used for the analyses.

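### The abstract names one primary outcome and the Outcomes section names four, each judged at p < 0.05 with no rule across them and no primary analysis set

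*Protocol article*

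**What the plan says.** The Methods/design part of the abstract is singular: "The primary outcome is weight loss". The Outcomes section is plural: "The primary outcomes will be reductions in body weight and BMI from baseline and reduction or maintenance of the prescribed energy and macronutrient intake", over the 4-week intervention. That names body weight, BMI, energy intake and macronutrient intake. The Hypocaloric diet section sets separate targets for carbohydrate, protein and fat ("The planned macronutrient profile will be 45–50% of total energy intake as carbohydrates", and so on), but nothing says whether each macronutrient gets its own primary test.

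The Data analysis section applies one threshold throughout: a p "value < 0.05 will be considered statistically significant". The only multiplicity step is inside each model: "All GEE models will be followed by a Bonferroni post hoc analysis and the least significant difference test".

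On analysis sets, the abstract says "All analyses will be done on a per-protocol and intention-to-treat basis". The Intervention procedures section repeats that both will be performed. Neither place ranks them.

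**The concern.** The primary outcome defines what the trial is judged on, and a reader cannot tell from this article whether that is one variable or several. With several primary outcomes, each tested at 0.05, and nothing said about how many must succeed, a significant result on any of them could be reported as success on the primary outcome. The two unranked analysis sets add a further choice.

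Two of the listed items are also poorly fixed:

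- **BMI.** The Anthropometric assessment section derives it from weight and height ("BMI will be calculated as weight (kg)/height" squared). Adult height does not change in 4 weeks, so BMI essentially repeats the weight test.
- **Intake.** A reduction in intake, or its maintenance at the prescribed level, does not settle which quantity is compared between arms. It could be change from baseline, deviation from the prescription, or the adherent/nonadherent class described under Hypocaloric diet.

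With about 28 participants, chance findings on single outcomes are easy to obtain and hard to tell from a real effect.

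**Working it through.** **Trial size.** The article states no familywise error rate, so the only figure of its own to reproduce is the sample size. For effect sizes f = 1.0, 0.8 and 0.6 at 80% power and alpha 0.05, the Sample size section gives 10, 12 and 20 subjects. A repeated-measures between-group F test with two groups, two measurements and correlation 0.5 (the last two are assumptions) returns exactly 10, 12 and 20. Adding 40% gives 20 × 1.4 = 28, which matches the randomisation blocks: 2 × 6 + 4 × 4 = 28, or 14 per arm.

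**Number of primary tests.**

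| Reading | Tests | Distinct tests, BMI merged with weight |
|---|---|---|
| Abstract | 1 | 1 |
| Outcomes section, as named | 4 | 3 |
| Outcomes section, macronutrients split in three | 6 | 5 |

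**Independent-test benchmark.** The chance of at least one p < 0.05 under no effect is 1 − 0.95^m:

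- m = 1: 5.0%
- m = 3: 14.3%
- m = 4: 18.5%
- m = 5: 22.6%
- m = 6: 26.5%

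Because BMI nearly duplicates weight, the relevant benchmarks are m = 3 and m = 5, not m = 4 and m = 6.

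**Correlated tests.** These come from a null simulation with 14 per arm, two-sided t tests, a weight–BMI correlation of 0.98 and other correlations from 0 to 0.7. The correlations are all assumptions, since the article gives none. The rule that any one significant outcome counts is also an assumption.

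| Items | At least one false positive, two-sided, one set | False claim of benefit, one set |
|---|---|---|
| Four named | about 12–16% | about 6–8% |
| Six (macronutrients split) | about 15–24% | about 8–12% |

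The last column is about half of the one before, because half of the false positives fall in the unfavourable direction.

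**Either analysis set may count.** Here the per-protocol set is assumed to be a random 10 of the 14 per arm. Correlations among the intake items run up to 0.7, and those between weight and intake up to 0.4. On this narrower grid the one-set figures are 13–15% (four items) and 17–23% (six). Letting either set count gives about 20–23% and 25–33%, roughly 1.4 to 1.5 times as high. For a single outcome the error rises from 5% to about 7%.

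**The case against.** The strongest reply is that the article gives no rule by which one significant outcome makes the trial positive. If all primary outcomes had to succeed, the error would be at most 5%. A decision rule and the ranking of analysis sets may also stand in a full analysis plan that is not shown. The first part stands as a limit on the percentages, which are conditional on the any-one-counts rule. Neither part removes the contradiction, because the choice of primary outcome is stated twice in this article, differently.

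A reader might go further than the text allows in several ways:

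- **At least five primary outcomes.** The Outcomes section names four. Five is reached only by splitting macronutrients and merging BMI with weight, and the article states neither step.
- **A fixed error rate of about 20%.** That figure needs split macronutrients or an either-set rule. It also counts false positives in both directions, whereas a falsely positive trial means a false claim of benefit.
- **Two analysis sets double the tests.** The sets share most participants, so they do not.
- **Per-protocol conditions on the mediator.** The Background hypothesises that stimulation works through better diet adherence, and the Hypocaloric diet section classifies adherence. No section defines the per-protocol set by that class, so this is a risk to avoid, not an error in the plan.
- **Intake cannot be compared between arms.** It can: weighed records at three times give mean energy and nutrient values, and a group-by-time model is planned. What is missing is the choice of quantity.

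It is also fair to say that the Abstract and Background both give the aim as weight loss together with food consumption. The conflict is over which outcomes are primary, not over the trial's general purpose.

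**Conclusion.** The point holds. The abstract and the Outcomes section contradict each other on the primary outcome. The stated 0.05 threshold is not controlled across the four named primary outcomes: the Bonferroni step works within each model and sits beside the unadjusted least significant difference test. No analysis set is primary. BMI adds almost nothing to weight, and the intake outcome is not fixed.

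If any one significant primary outcome counts, the two-sided error in one set is about 2.4 to 3.2 times the nominal 5% for the four named items (12/5 to 16/5). It is larger if macronutrients are split or if either set may count. The size rests on that rule, on the assumed correlations and on 14 per arm. The contradiction rests on no assumption.

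**What to change.** Before unblinding, bring the abstract and the Outcomes section into line:

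1. **Primary analysis.** Between-arm difference in change in body weight (kg) from baseline to the end of week 4, in all randomised participants by intention to treat, at two-sided 0.05.
2. **Secondary outcomes.** BMI, energy intake expressed as recorded minus prescribed kcal/day, and macronutrient intake.
3. **Per-protocol.** A sensitivity analysis only. If the set is defined, do not base it on diet adherence, which is the hypothesised pathway.

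If the investigators want to keep several primary outcomes, they must state a hierarchy or split alpha. Bonferroni over four (0.0125 each) gives 1 − 0.9875^4 = 4.9% for independent tests, but lowers the power of each test.

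The change is mostly wording, but it has a real cost. Intake loses primary status, and the Sample size section rests on calories ingested. That calculation then does not support the primary outcome, and recruitment has already started. The text should say plainly that power for weight was not calculated.

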##### Assessment of glycemic variability

Glycemic variability will be assessed using the FreeStyle® Libre™ Flash Glucose Monitoring System. This factory-calibrated interstitial glucose monitoring system uses a wired glucose oxidase enzyme coimmobilized on an electrochemical sensor that is worn on the back of the arm for up to 14 days [43]. Participants can obtain a real-time reading every minute by scanning the sensor with a reader. The data are transferred from the sensor to the reader memory and recorded automatically every 15 minutes. Glucose trends, rates, and direction for the past 8 hours are shown on the screen and can be uploaded to a computer for summary reports. The participants’ sensor data will be uploaded using FreeStyle® Libre™ version 1.0 software and will be saved into five files: one general file and one for each of the 4 weeks of treatment.

The mean amplitude of glycemic excursion (MAGE), which is the mean of blood glucose values exceeding 1 SD from the 24-hour mean blood glucose value, will be used as an index of glycemic variability [44]. To adapt MAGE for interstitial glucose, glucose values will be captured at 2-hour intervals from the minimum and maximum points of the glucose excursion plot. WebPlotDigitizer version 3.12 [45] will be used to calculate the minimum and maximum mean glucose values. This software accurately transforms a variety of plot types and images into numeric data.

A subgroup of individuals enrolled in this study will receive a FreeStyle® Libre™ unit to be used during the course of the 4-week intervention. Two sensors will be required to monitor each participant: The first will be placed on the first day of the intervention, 1 hour before the first tDCS session; the second will be placed after 14 days. A trained researcher will place the sensors on the participants according to the manufacturer’s instructions and will provide a brief explanation of their operation. For this trial, the participants will be instructed to check the sensor at least eight times daily: after waking up; just before and 2 hours after breakfast, lunch, and supper; and before sleeping.

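### The exploratory MAGE outcome has no pre-treatment baseline to compare with, and its stated formula gives a glucose level, not an excursion amplitude

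*Protocol article*

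**What the plan says.** The Outcomes section of the protocol article places "changes in glycemic variability, such as reduced MAGE compared with baseline" among the exploratory outcomes.

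The section Assessment of glycemic variability describes how the data arise:

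- A subgroup "will receive a FreeStyle® Libre™ unit to be used during the course of the 4-week intervention"; the Design overview likewise ties the monitor to the intervention.
- On the first of two sensors: "The first will be placed on the first day of the intervention, 1 hour before the first tDCS session". The second follows after 14 days. Each sensor is "worn on the back of the arm for up to 14 days".
- The data are saved as "one general file and one for each of the 4 weeks of treatment".
- MAGE is expanded as a mean amplitude of glycemic excursion and then defined: "which is the mean of blood glucose values exceeding 1 SD from the 24-hour mean blood glucose value".
- On recording: "The data are transferred from the sensor to the reader memory and recorded automatically every 15 minutes".
- For the calculation, "glucose values will be captured at 2-hour intervals from the minimum and maximum points of the glucose excursion plot", using plot-digitising software.

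The Intervention procedures section has the diet prescribed when the baseline evaluation ends, and the Randomization section puts allocation after that prescription.

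**The concern.** Two statements in the plan do not work.

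First, the outcome is a change from baseline, but no monitoring period before treatment is described and no part of the treatment period is named as the baseline. An analyst would have to drop the comparison or choose an early treated window after the fact. Such a window already contains diet and stimulation, so any effect that has begun by then would be subtracted from the result. The article's own Background cites a reduction in caloric intake of about 32% after a single session, so an early effect is plausible on its own premises.

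Second, the formula averages glucose values that lie far from the daily mean. That is a level. All participants follow a hypocaloric diet and the trial looks for lower glucose, so an index that follows level could be reported as reduced variability when only mean glucose has fallen.

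**Working it through.** The plan gives no figure for this outcome, so there is none to reproduce. The checks are schedule arithmetic, an algebraic property of the formula, and an illustration on assumed profiles.

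**1. Is there a baseline?** Inputs from Assessment of glycemic variability: 15-minute recording, placement one hour before the first session, two sensors of up to 14 days.

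- Readings per day: 24 × 60 / 15 = 96.
- Readings before the first session: at most 60 / 15 = 4.
- Sensor days available: 2 × 14 = 28, which the 4 × 7 = 28 treatment days use up.
- Saved files: one general and four treatment-week files, none for baseline.

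Four readings cannot supply the 24-hour mean and SD that the definition requires. The baseline liquid meal test cannot stand in: it has eight glucose samples from −30 to 240 minutes, a span of 4.5 hours. If week 1 were taken as baseline, it would contain 5 of the 20 sessions.

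**2. What does the formula measure?** Let the day's readings be g₁ … g₉₆, with mean m and standard deviation s. The index as worded is the mean of those gᵢ with |gᵢ − m| > s. Add a constant c to every reading. Then m becomes m + c, s is unchanged, the same readings are selected, and the index becomes index + c. Every peak-to-nadir difference is unchanged. The index therefore moves one-for-one with glucose level, whatever the profile.

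Illustration (assumed profiles, not from the documents): a flat basal level plus three meal peaks at 8, 13 and 20 h, each of height A × exp(−((t − meal time)/0.75)²), with t in hours, read every 15 minutes, in mg/dl.

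| Basal level | Peak height A | Index as worded | Mean peak-to-nadir difference > 1 SD |
|---|---|---|---|
| 90 | 50 | 130.7 | 50.0 |
| 110 | 50 | 150.7 | 50.0 |
| 110 | 25 | 130.4 | 25.0 |

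Rows 1 and 2: swings identical, index differs by 20. Rows 1 and 3: amplitude differs twofold, index nearly equal. Counting only readings above the mean plus 1 SD gives the same figures on these profiles.

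**3. Does 2-hour capture matter?** It depends on the reading.

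- *One value every 2 hours:* 24 / 2 = 12 of 96 readings, or 12.5%. On one assumed day with peaks of about 2.0–2.4 mmol/L, the 15-minute amplitude is 2.29 and the 2-hour grids give 1.65 to 1.92. These are 1 − 1.92/2.29 = 16% to 1 − 1.65/2.29 = 28% too low. Across other assumed peak widths and grid positions the error ran from about −36% to +8%. On the first profile in the table it was negligible (49.98 against 50.00), because a peak that falls between grid points there stays below the 1 SD threshold and drops out of the average.
- *Minimum and maximum within each 2-hour interval:* on assumed three-meal days this reproduced the 15-minute amplitude to within 0–0.5%.

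**The case against.** The strongest reply has four parts.

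*The between-arm comparison survives.* The Data analysis section models group, time and their interaction by GEE and reports marginal means per group at each time point. Four weekly files fit that model. This stands: a reader might infer that the trial can say nothing about glycemic variability, and the documents do not support that. Only the comparison with baseline fails. Nor does any section say that a treated window will serve as baseline, so the subtraction of an early effect is a risk of the gap and not a stated plan.

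*The formula is loose wording.* The sentence is a one-line paraphrase with a citation, the index is named as an amplitude, and the next sentence works from minima and maxima. Amplitudes may well be intended. But no peak-to-nadir difference is defined anywhere, and the only definition given is of something else. The wording needs correcting even if the intention is sound. The documents do not show that the literal formula will be the one run.

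*The plot reading is misjudged.* A reader might infer that a 2-hour grid misses post-meal peaks and understates MAGE by 16–28%. The text does not support that as a finding. It refers to minimum and maximum points, which can mean the extremes within each interval, and that reading loses almost nothing. The article also links uploading to summary reports and saved files, and does not say that the 15-minute values can be exported as numbers.

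*The outcome is minor.* It is exploratory and measured in a subgroup. This stands and limits the weight of the point. That MAGE is offered as an example does not help, because the sensor is the only source described for glycemic variability and MAGE the only index.

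**Conclusion.** The point holds in two parts. The comparison with baseline cannot be computed, because at most 4 of 96 daily readings precede stimulation and both sensors are used up by the 28 treatment days. This rests on the stated schedule alone. The formula as worded measures glucose level: it shifts by exactly the change in level while amplitude stays fixed. That is algebra and needs no assumption; only the table's values depend on assumed profiles.

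The 2-hour capture is an ambiguity to clear up, with no established bias. The understatement of 16–28% applies only if a single value is taken every 2 hours, and only on one assumed day.

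The consequence is confined to one exploratory outcome in a subgroup. Primary and secondary outcomes and the sample size are not affected.

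**What to change.** - **Outcome.** Replace the comparison with baseline by the active-minus-sham difference in on-treatment MAGE, either by week within the planned GEE model or averaged over weeks 1–4, with no baseline term. If weekly values are used, name the group difference as the quantity of interest. The group-by-time term alone tests whether the difference changes across the weeks, and would miss an effect that is present from week 1 and then constant.
- **Definition.** State MAGE as the mean of peak-to-nadir glucose differences that exceed 1 SD of that day's glucose.
- **Data capture.** State that the true minima and maxima are used. Confirm whether the recorded 15-minute values can be exported and, if so, compute MAGE from them in place of the plots.

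This costs rewording and minor analysis work, with no new visits, sensors or participants. What is given up is the within-person claim against baseline, and with it any precision that a baseline value would have added. The comparison also assumes that monitored participants were chosen without regard to arm, which the article does not describe and the report should state.
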